#### Intervention With an Adaptive Engagement Design

Participants will be asked to use their app daily for 30 days. Adherence to the intervention (ie, ongoing app usage) will be promoted via 2 main methods. First, all participants will receive daily in-app push reminders to use the app as described above. Second, adherence will be automatically monitored, and additional support will be triggered via an adaptive engagement design: after any 2 consecutive days of nonuse, participants will be sent a text message encouraging re-engagement with the app. After approximately 1 week of nonuse, participants will receive a phone call from staff on the closest business day, during which staff will help identify and troubleshoot barriers to adherence. This pattern will repeat for up to approximately 2 weeks, at which point there will be a final phone call attempt before discontinuing texts and calls to reduce the potential for unwanted burden.

#### Second EMA Burst

In advance of the final intervention week, study staff will contact each participant to provide instructions for completing their second EMA burst, which will be scheduled to coincide as closely as possible with the fourth week of the intervention. Staff will meet virtually with participants to refresh their EMA training, including reviewing any barriers and facilitators to EMA adherence identified after their baseline burst. The second EMA burst is intended to begin immediately after the call and continue for 7 days. It will follow the same procedures as at baseline.

#### Posttest Visit

Participants will meet virtually with study staff for a posttest visit occurring approximately 1 month after the start of app use (ie, as close as possible to the end of the 30-day app path). This will mirror the baseline visit procedures except that (1) the posttest questionnaire will measure health outcomes and potential covariates since the last assessment and will include an assessment of implementation outcomes, (2) there will be a posttest qualitative interview, and (3) there will be a debrief of the second EMA burst, during which staff solicit feedback on any refinements participants suggest to the procedures.

The posttest qualitative interview will probe 3 main domains: app implementation (eg, determinants of app adherence, acceptability, and penetration), any perceived effects of the app, and suggestions for future refinements. Wherever possible, questions will be worded identically across arms. Staff will be trained to conduct the interviews through didactic instruction, role-playing, and supervised practice, focusing on techniques such as open-ended questions, active listening, and probing for depth while minimizing interviewer bias [26]. Proficiency will be assessed through mock interviews and iterative feedback. The interviews will be audio recorded, securely stored, and transcribed for qualitative coding. At the conclusion of the interview, staff will invite the participant to retain the app on their phone until the 6-month follow-up. All participants will receive automated text messages from the study team once monthly to promote retention.

#### 6-Month Follow-Up Visit

The remote 6-month follow-up visit will be comprised only of the 6-month follow-up questionnaire. The questionnaire will be administered via REDCap using the same procedures as during the baseline and posttest visits. It will measure health outcomes and potential covariates since the last assessment.

### Outcomes

Both quantitative and qualitative data will be collected. Table 1 summarizes the primary and secondary quantitative outcomes along with potential moderators and covariates. As described above, qualitative themes that will be probed in posttest interviews to complement and contextualize the quantitative data will include determinants of app implementation, perceived effects of the apps, and suggestions for future refinements.

**Table 1 table1:** Quantitative outcomes for the hybrid type 2 pilot randomized controlled trial (RCT).

Outcome				Measure		Time point		Source
**Primary outcome**								
	App adherence		Days of objective app usage		Intervention		App analytics	
**Secondary implementation outcomes**								
		Acceptability	Acceptability of Intervention Measure (AIM) [27]		1 month		Questionnaire	
		Appropriateness	Intervention Appropriateness Measure (IAM) [27]		1 month		Questionnaire	
		Feasibility	Feasibility of Intervention Measure (FIM) [27]		1 month		Questionnaire	
		Usability	System Usability Scale (SUS) [28]		1 month		Questionnaire	
		Satisfaction	Client Satisfaction Questionnaire CSQ-8) [29]		1 month		Questionnaire	
		Penetration	In-app referral to AIM+ RCT^a^		Intervention		App analytics	
		Penetration-youth	In-app referral to AIM RCT for youth		Intervention		App analytics	
		Penetration-youth	Files for youth played in AIM+ or Resource+		Intervention		App analytics	
**Secondary health outcomes**								
		Anxiety	PROMIS^b^ v1.0 Anxiety (standard computer adaptive test) [30]		Baseline, 1 month, 6 months^c^		Questionnaire	
		Depression	PROMIS v1.0 Depression (standard computer adaptive test) [30]		Baseline, 1 month, 6 months		Questionnaire	
		Workplace burnout	Maslach Burnout Inventory–General Survey (MBI-GS) [31]		Baseline, 1 month, 6 months		Questionnaire	
		Perceived stress	Perceived Stress Scale (PSS) [32]		Baseline, 1 month, 6 months		Questionnaire	
		Anger	PROMIS Short Form v1.1 Anger [30]		Baseline, 1 month, 6 months		Questionnaire	
		Sleep disturbance	PROMIS Short Form v1.0 Sleep Disturbance [33]		Baseline, 1 month, 6 months		Questionnaire	
		Alcohol use	PROMIS v1.0 Alcohol Use [34,35]		Baseline, 1 month, 6 months		Questionnaire	
		Resilience	Brief Resilience Scale (BRS) [36]		Baseline, 1 month, 6 months		Questionnaire	
		Mindfulness	Five Facets of Mindfulness Questionnaire (FFMQ-15) [37-39]		Baseline, 1 month, 6 months		Questionnaire	
		Attentional control	Attentional Control Scale (ACS) [40]		Baseline, 1 month, 6 months		Questionnaire	
		Emotion regulation	Negative Mood Regulation (NMR) [41]		Baseline, 1 month, 6 months		Questionnaire	
		Current mood states	International Positive Affect Negative Affect Schedule Short Form (I-PANAS-SF) [42,43]		Baseline, last intervention week		EMA^d^	
		Current attention	2 items adapted from Chin et al [44]		Baseline, last intervention week		EMA	
**Moderators and covariates**								
	Demographics		Gender, age, race and ethnicity, education, household income		Baseline		Questionnaire	
	Employment		Length of current employment, role		Baseline		Questionnaire	
	Mental health treatment history		Psychotherapy, hospitalization, psychotropic medication		Baseline, 1 month, 6 months		Questionnaire	
	Other meditation		Meditation practice frequency and type		Baseline, 1 month, 6 months		Questionnaire	

^a^RCT: randomized controlled trial.

^b^PROMIS: Patient-Reported Outcomes Measurement Information System.

^c^1 month and 6 months: 1-month follow-up (ie, posttest) and 6-month follow-up, respectively.

^d^EMA: ecological momentary assessment.

The primary outcome of the pilot RCT will be app adherence per objective analytics data. A total of 2 main operationalizations will be considered. First, following other pilot RCTs of health apps [45], we aim for >60% of participants to open the app on at least 1 day after their randomization visit. Second, we will examine the mean number of content files played over the course of the intervention. Although there is no established dosage for app-based meditation [46], meditation studies have observed positive effects on mental health after 2 weeks, including for brief, audio-guided mindfulness practices [47]. Accordingly, we will explore if participants complete an average of 14 daily path files, and if this benchmark appears to be met within some subsets of participants but not others to help contextualize the findings and inform future work.

Secondary implementation outcomes will include acceptability, appropriateness, and feasibility as measured by the Acceptability of Intervention Measure (AIM), Intervention Appropriateness Measure (IAM), and Feasibility of Intervention Measure (FIM) [27], respectively; usability as measured by the System Usability Scale (SUS) [28], satisfaction as measured by the Client Satisfaction Questionnaire (CSQ) [29], and penetration as indicated by objective analytics (ie, in-app referral to our RCTs of AIM+ for professionals and AIM for youth, and files played for youth by professionals using their study app).

All health effects will be treated as secondary outcomes. In accordance with our sponsor guidelines, the purpose of this data collection will be to ensure its feasibility in preparation for a future, fully-powered trial if justified by the present design [48]. That future trial would focus on group differences in anxiety and depression symptoms as measured by the Patient-Reported Outcomes Measurement Information System (PROMIS) v1.0 Anxiety and Depression scales, respectively [30], workplace burnout as measured by the Maslach Burnout Inventory-General Survey (MBI-GS) [31], and perceived stress as measured by the Perceived Stress Scale (PSS) [32]. It will also explore changes in anger, sleep disturbance, and alcohol use as measured by the PROMIS Short Form v1.1 Anger [30], PROMIS Short Form v1.0 Sleep Disturbance [33], and PROMIS v1.0 Alcohol Use [34,35] scales; in resilience as measured by the Brief Resilience Scale (BRS) [36]; in mindfulness as measured by the Five Facets of Mindfulness Questionnaire (FFMQ-15) [37-39]; and in attentional control as measured by the Attentional Control Scale (ACS) [40]. The primary mechanistic target—emotion regulation—will be assessed both retrospectively via the Negative Mood Regulation (NMR) scale [41] and in real time via EMA reports that include a short form of the International Positive Affect Negative Affect Schedule (I-PANAS-SF) [42,43]. A real-time assessment of attentional control will also be included in the EMA reports using 2 items adapted from Chin and colleagues [44]. Data collection will be considered feasible if at least 70% of participants complete the questionnaire measures at 1 and 6 months, and if participants fill out an average of at least 70% of the EMA reports at each burst. EMA reports will be counted if they are completed in full. We will also examine partial EMA completion rates during the pilot RCT and, as relevant, probe barriers to fully completing the EMA reports during the qualitative exit interviews with participants.

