**Objective:**

This paper describes the protocol for a hybrid type 2 effectiveness-implementation pilot randomized controlled trial (RCT) of Bodhi AIM+, a meditation app adapted with and for professionals who work with youth in the legal system. The adaptation process and implementation plan, as well as the pilot RCT design, were guided by theoretically driven implementation science frameworks. The primary outcome of the pilot RCT is app adherence (ie, ongoing app usage per objective analytics data).

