The process of adapting and implementing Bodhi for officers and other professionals was guided by the EPIS (Exploration Preparation Implementation Sustainment) and CFIR (Consolidated Framework for Implementation Research) implementation science frameworks [15-17]. We collaborated with stakeholders to identify key determinants (ie, barriers and facilitators) of professionals’ adherence to the app and develop corresponding implementation strategies to promote adherence. Adherence (ie, ongoing app usage) was identified as the primary outcome because low adherence to health apps is a pervasive issue and adequate levels are a precondition to achieving health benefits [18]. The implementation strategies that were developed included tailoring the meditation practices for relevance to officers and other professionals during their workday (eg, practices for before a meeting or before court), recording the practices with a guide stakeholders found appealing and trustworthy, and building an automated adaptive engagement design to detect low app adherence based on analytics data and trigger additional support (eg, text messages, as detailed below). All of this was accomplished through an iterative series of qualitative interviews with officers rooted in the EPIS and CFIR frameworks. These formal interviews were supplemented by ongoing feedback from a range of other stakeholders including leadership in the juvenile legal system, youth with experience in the legal system, meditation experts, and the AIM+ Community Advisory Board (CAB). The AIM+ CAB comprised adults with backgrounds relevant to studying AIM+ including working in the juvenile legal system, youth services, meditation instruction, and community mental health.

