## Discussion

This hybrid type 2 effectiveness-implementation pilot RCT of the AIM+ meditation app will integrate quantitative and qualitative data to evaluate app adherence (ie, ongoing app usage) and explore other implementation outcomes, as well as related barriers and facilitators to implementation. It will include an in-depth assessment of health outcomes, including real-time capture of the mechanistic target (ie, emotion regulation), allowing for evaluation of the feasibility of this data collection and setting the stage for a fully-powered RCT if justified by the present pilot findings.

The AIM+ meditation app was built with and for officers and other professionals who work with youth in the legal system to make authentic mindfulness meditation practices available throughout the workday. It is a direct response to requests from stakeholders for such an intervention, created in collaboration with our community partners by adapting an existing meditation app, Bodhi, for use by the target audience. The adaptation process and implementation plan—as well as the pilot RCT detailed in this protocol paper—were guided by the EPIS and CFIR implementation science frameworks [15-17].

Consistent with pilot RCTs of other health apps [45], we expect that >60% of participants will open the app at least 1 day after their randomization visit per objective analytics data, and we will explore the mean total number of content files played over the course of the intervention. We further expect that our longitudinal assessments of health outcomes will be feasible, as evidenced by at least 70% of participants completing the questionnaire measures at each follow-up time point and at least 70% of the EMA reports being completed within each week-long EMA burst.

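### The only adherence figure set as an aim measures one-off uptake, although the primary outcome is defined as ongoing use and tabulated as days of use

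*Protocol article*

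**What the plan says.** The Abstract (Objective) states: "The primary outcome of the pilot RCT is app adherence (ie, ongoing app usage per objective analytics data". The Introduction explains why adherence was chosen: "low adherence to health apps is a pervasive issue and adequate levels are a precondition to achieving health benefits". Table 1 lists the primary measure as "Days of objective app usage", taken from app analytics over the intervention.

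The Outcomes text after Table 1 then says "A total of 2 main operationalizations will be considered". The first is "we aim for >60% of participants to open the app on at least 1 day after their randomization visit". The second is the mean number of content files played, which the authors will explore against an average of 14 daily path files, overall and in subsets.

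The Discussion carries forward only the first as an expectation: "we expect that >60% of participants will open the app at least 1 day after their randomization visit". It again describes the file count as something to be explored. This sentence also drops a word (on), so it can be read as a statement about timing rather than about a number of days.

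**The concern.** Three descriptions of one primary outcome do not agree. The definition speaks of continuing use, the table of a count of days, and the stated aim of whether the app was ever opened. Cutting a count of days at 1 discards exactly the information that separates continuing use from a single try.

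The protocol's own engagement rules show the mismatch. In the section on the adaptive engagement design, two consecutive days without use trigger a text message and about a week without use triggers a staff call. A participant who opens the app once and never returns would pass through that sequence as a nonuser, and would still count towards meeting the aim.

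At stake is what the pilot can say about adherence. The protocol selected adherence because adequate use is needed before any benefit can follow, and the results are meant to inform whether a fully powered trial is justified. An aim that can be met with almost no continuing use does not inform that question.

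**Working it through.** **Inputs from the protocol article.** Planned sample 50, so 25 per arm at 1:1 (Overview; Randomization Visit). Daily use is requested for 30 days (Intervention With an Adaptive Engagement Design). Day 1 of the path is played with staff at the randomization visit and falls outside the aim, which leaves 29 days. The sample size is described as pragmatic, so there is no power figure to reproduce.

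**Step 1: the least use that meets the aim (no model needed).**
- 0.60 × 50 = 30, so exceeding 60% takes 31 people: 31/50 = 62%.
- If each opens the app once, mean use is 31 × 1/50 = 0.62 days.
- As a share of requested person-days: 31/(50 × 30) = 31/1,500 = 2.1%.
- Opening is enough, so the number of files played after the visit could be zero.
- The text does not say whether the aim applies to both arms pooled or to one. For one arm of 25, 16 openers are needed: 16/25 = 64%, mean 0.64 days.

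**Step 2: an illustrative model (assumption).** Let each person open the app with the same probability q on each of 29 days, independently. The chance of ever opening is 1 − (1 − q)^29.
- Setting this to 0.60 gives q = 1 − 0.4^(1/29) = 0.0311, a mean of 29 × 0.0311 = 0.90 days.
- The chance of meeting the aim is the binomial probability of at least 31 of 50 (or 16 of 25):

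| q per day | Mean use-days | Ever opened | Aim met, n = 50 | Aim met, n = 25 |
|---|---|---|---|---|
| 3% | 0.87 | 58.7% | 37% | 37% |
| 4% | 1.16 | 69.4% | 90% | 79% |
| 5% | 1.45 | 77.4% | 99.6% | 96% |

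Real use varies between people. For the same mean, concentrating use in fewer people lowers the ever-opened rate, so these probabilities illustrate and do not predict. Step 1 does not depend on the model.

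**Step 3: does the second operationalization supply the missing measure?**
- Fourteen files are 14/30 = 47% of the path, far above the use that meets the aim. A reported mean would therefore expose the situation in Step 1.
- Files are not days. The description of the AIM+ app says that finishing one practice unlocks the next, and it states no limit of one per day.
- A mean can hide the spread. If 24 of 50 people complete all 30 files and 26 complete none, the mean is 24 × 30/50 = 14.4, above 14, although more than half did nothing. Crediting those 26 with the staff-guided Day 1 file gives (720 + 26)/50 = 14.92.
- No rule ranks or combines the two operationalizations.

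**The case against.** The strongest reply is that the aim should not be read alone. The same paragraph sets a dose-related benchmark of 14 path files, gives a rationale for it, and plans to see which subsets reach it. Near-zero use would show there at once. The words used are aim and expect, in a descriptive pilot whose conclusions also draw on acceptability, usability, data-collection feasibility and interviews. The 60% figure follows other pilot trials of health apps, it leaves out the staff-guided first session, and the reminders are part of the implementation strategy under study.

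Much of this stands, and it rules out several stronger readings:
- A reader might infer that days of use will never be reported. The Data Analysis section introduces its examples with eg, and the Outcomes text speaks of two main operationalizations, so neither excludes such a report.
- A reader might infer a formal go/no-go rule under which the pilot would be declared a success. None is stated.
- A reader might take 14 days as the protocol's own adherence threshold. The benchmark is 14 files.
- A reader might treat openings of the Youth or Help pages as wrongly counted. Excluding them is a preference; supporting youth was one of the purposes for which officers asked for the app.

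What the reply does not remove is the mismatch itself. The file count is exploratory in both places where it appears, and missing it would not change whether the stated aim is met. Precedent may support 60% as a figure for uptake, but it does not turn uptake into continuing use.

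**Conclusion.** The point holds in this form: the article defines adherence as ongoing use and tabulates it as days, but the only figure it aims for is an ever-opened rate. That aim can be met with 31 single openings among 50 people, a mean of 0.62 use-days and 2.1% of the requested person-days. This minimum rests only on the planned sample of 50 and the wording of the aim. The figure of about 3.1% per day (mean 0.9 days) for 60% ever-openers rests on an assumed constant, independent daily probability. The file count would reveal low use but is exploratory, is not a count of days and is unranked against the aim. This is not detail left to a fuller document, because the article itself fixes both the measure and the aim, and they disagree.

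**What to change.** Before outcome data are examined:

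1. Make Table 1's measure the primary adherence outcome: the number of distinct days on which the participant used the app, from after the randomization visit through day 30. Report its distribution by arm.
2. Report beside it the proportion of participants who complete at least 14 daily path files, which keeps the protocol's own benchmark in its own unit. If a threshold in days is also wanted, label it as a new choice.
3. Keep the 60% figure as a separate outcome labelled uptake or initiation.
4. Align Table 1, the Outcomes text, the Discussion (including the dropped word) and the registry entry.

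Whether Youth or Help openings count as use is optional and not part of the correction.

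**Cost.** No new data are needed, because opening and closing times are already recorded for each app feature. The change would need review by the IRB, the independent monitoring committee and the sponsor while enrollment is under way, plus a registry update. The headline figure will probably look less favourable than an ever-opened rate.

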### App-Based Interventions

#### Bodhi AIM+

The AIM+ app—officially named Bodhi AIM+ to recognize its connection to the Bodhi app from which it was adapted—is a meditation app for professionals working with youth in the legal system. It includes 5 main parts: Home, Favorites, To Go, Youth, and Help (see Figure 2 for prototype screenshots). The Home page features a 30-day path of brief (approximately 5- to 10-minute) audio-guided meditations with videos interspersed to promote engagement. Users are encouraged to follow 1 of the practices each day for a month. To unlock the next practice, a user must first play the current practice to completion; once unlocked, users can scroll forward or backward to replay practices as desired. They can also tap a heart icon on any of the daily path practices; these practices will then appear in the Favorites part of their app for easy access. In addition to following the 30-day path, users can select from a menu of To Go audio-guided meditations to prepare for specific situations (eg, attending a meeting). Users also have access to a menu of To Go audio-guided meditations designed with and for youth in the legal system and featured in the original AIM app for young people (eg, meditations for before going to a party or to court). Users are invited to play these practices for any youth who might find them beneficial. Finally, the Help tab in AIM+ serves 2 main functions. First, users can use this part of the app to contact study staff by phone or text for support. Second, the Help tab includes referral buttons for users to share opportunities to participate in clinical trials research of AIM+ and AIM with colleagues and youth, respectively. These buttons auto-populate text messages that provide the recipient with a link to the relevant IRB-approved study flier where they are presented with more information. Users are instructed not to inquire further with peers or youth if they decide to participate to minimize the potential for coercion.

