#### Randomization Visit

Study staff will meet again virtually with each participant after the baseline EMA burst. Staff will review the total percentage of EMA surveys completed and discuss any issues with compliance, including any potential solutions for the second EMA burst based on their experience. Participants will then be individually randomized via REDCap to the AIM+ or Resource+ app at a 1:1 ratio. The allocation sequence will be generated in advance by the data manager under the supervision of a biostatistician and loaded into REDCap, where it will be fully concealed from the research team. Research staff will use the randomization module in REDCap to assign allocations, but will not be able to see the schedule or view allocations until they are assigned. Both staff and participants will thus be blind to arm through the completion of all baseline assessments. Next, staff will guide participants in downloading their relevant app and playing Day 1 of the 30-day path, which provides a video-guided introduction to the app. Participants will be encouraged to follow the 30-day path by playing a brief path file each day, and invited to use the other app features as desired; for details on the app content, see the AIM+ and Resource+ descriptions above. Participants will be trained not to use their app when doing so could interfere with work, be dangerous, or be embarrassing. Staff will guide participants in planning for when they will be most successful in using the app and then schedule personalized daily in-app push reminders based on those times.

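### The exploratory 14-file adherence benchmark is a group mean, so it can be met while most participants complete fewer than 14 path files

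*Protocol article*

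**What the plan says.** The Outcomes section (text after Table 1) gives app adherence two operationalizations. The first aims for more than 60% of participants to open the app on at least one day after the randomization visit. For the second, "we will examine the mean number of content files played over the course of the intervention". The benchmark follows: "we will explore if participants complete an average of 14 daily path files". The same sentence adds that the authors will see whether the benchmark appears to be met in some subsets and not in others, to give context and inform later work.

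The reason given for 14 is that "meditation studies have observed positive effects on mental health after 2 weeks, including for brief, audio-guided mindfulness practices". The authors also state that no dosage is established for app-based meditation.

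The Bodhi AIM+ section describes a "30-day path of brief (approximately 5- to 10-minute) audio-guided meditations with videos interspersed to promote engagement". On pace it says "Users are encouraged to follow 1 of the practices each day for a month", and on access "To unlock the next practice, a user must first play the current practice to completion". At the randomization visit, staff guide each participant in "playing Day 1 of the 30-day path, which provides a video-guided introduction to the app". Table 1 lists the adherence measure as days of objective app use.

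**The concern.** The rationale concerns how long people practise before benefit is seen. The benchmark concerns the average number of files across a group. The two agree only if participants cluster around the average. Use counts on a path capped at 30 files, in a field where the Introduction itself calls low adherence pervasive, may instead split into people who finish and people who stop early. The mean then describes neither group.

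This benchmark is the only part of the primary outcome tied to an amount of use; the other part asks for one opening of the app. The Introduction treats adequate adherence as a precondition for health benefit, and the pilot is meant to inform a fully powered trial. A reader told that the average reached 14 could conclude that participants typically had about two weeks' worth of content when most had less.

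**Working it through.** **Inputs.** Path length 30 files, about 5 to 10 minutes each (Bodhi AIM+ section). Benchmark 14 (Outcomes). Sample size 50 (Methods, Overview). Allocation 1:1 (Randomization Visit), taken here as 25 per arm. The article gives no distribution of use, so the patterns below are possibilities, not forecasts.

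**Step 1: reproduce the figure.** 2 weeks × 7 days × 1 file per day = 14. The figure reproduces at the encouraged pace of one file a day.

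**Step 2: two-group patterns.** Let *k* of *n* people complete all 30 files and the rest complete *L*. The mean is [30*k* + *L*(*n* − *k*)]/*n*. It reaches 14 when *k* ≥ *n*(14 − *L*)/(30 − *L*). The smallest such *k* gives:

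| *n* | *L* | *k* | Mean | Below 14 |
|---|---|---|---|---|
| 25 | 1 | 12 | (360 + 13)/25 = 14.92 | 13/25 = 52% |
| 25 | 7 | 8 | (240 + 119)/25 = 14.36 | 17/25 = 68% |
| 25 | 13 | 2 | (60 + 299)/25 = 14.36 | 23/25 = 92% |
| 50 | 1 | 23 | (690 + 27)/50 = 14.34 | 27/50 = 54% |
| 50 | 7 | 16 | (480 + 238)/50 = 14.36 | 34/50 = 68% |
| 50 | 13 | 3 | (90 + 611)/50 = 14.02 | 47/50 = 94% |

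In the rows with *L* = 13 the others fall only one file short, so those rows show how little the mean says about a threshold rather than a serious shortfall. The rows with *L* = 1 and *L* = 7 matter more.

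**Step 3: smooth dropout.** Suppose everyone plays file 1 and goes on from each file to the next with constant probability *q*. The mean is the sum of *q*^(*j* − 1) for *j* = 1 to 30, that is (1 − *q*^30)/(1 − *q*). Setting this to 14 gives *q* = 0.9396. The share reaching file 14 is *q*^13 = 0.445, about 44%, and the median is about 12 files.

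**Step 4: does leaving out Day 1 solve it?** With 29 files left and a mean of 14 still required, 12 of 25 at 29 files and 13 at 1 give (348 + 13)/25 = 14.44, with 52% below 14. The weakness comes from the mean, not from Day 1.

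**Step 5: the reverse error.** If 13 of 25 complete 14 files and 12 complete 1, the mean is (182 + 12)/25 = 7.76. Most people reach 14 and the benchmark fails. The mean can mislead in either direction.

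**The case against.** The strongest reply is that this is a descriptive yardstick. The authors say they will explore it, concede that no dosage is established, and state an expectation in the Discussion only for the opening of the app. They also anticipate uneven use by planning to look within subsets. Table 1 lists days of use, so use packed into a few days would be visible there. The two-week statement reports what studies found over a period and does not set an individual dose. The two-group splits are extremes, and the smoother pattern gives a median of about 12, a modest gap.

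Most of this stands, and it limits the point. It does not remove it: the subset look applies the same benchmark to smaller groups, and days of app use do not show how many people completed 14 path files.

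Several stronger readings are tempting but unsupported:

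- *Meeting the benchmark would license the full trial.* No passage ties it to progression.
- *The staff-guided Day 1 file inflates the count.* The file benchmark states no exclusion like that in the first operationalization, but nothing says that Day 1 counts. It could add at most 1 file per person.
- *Participants can race through the path.* Completing the current file is the only unlock condition given, but a condensed article may omit a calendar lock.
- *Content files and path files contradict each other.* They read as a general measure and a narrower benchmark within it.
- *Videos should not count.* Adherence is defined as ongoing app use, so counting them fits the definition.

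**Conclusion.** The point holds as a limited one. The benchmark's group mean does not show whether participants reached the amount of use that motivates it. In the patterns worked here it is met with 52% to 94% of people below 14, and with constant dropout about 56% (100% − 44%) fall short. These sizes rest on assumed patterns of use and, for the arm-level figures, on 25 per arm. The arithmetic shows what the mean permits, not what will happen.

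A reader might infer that the adherence assessment as a whole is unsound or that readiness for the next trial will be overstated. The article does not support that: the benchmark is exploratory, there is no go/no-go rule, and days of use are measured as well. The change is worth making because this is one of two operationalizations of the primary outcome, and a per-person summary costs almost nothing.

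**What to change.** Keep the mean number of files and add a per-person criterion as the basis for judging the benchmark:

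- Report, by arm, the proportion of participants completing at least 14 distinct daily path files, so that replays do not count.
- Report the median and interquartile range with the mean.
- Count only files played after the randomization visit, in line with the first operationalization, and say so.
- Apply the meditation-based rationale for 14 to AIM+ only; Resource+ contains no meditation, so its figure is a comparison of engagement.
- Show distinct days of path use alongside, since Table 1 already lists days of app use.

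Leaving out the videos, or requiring the 14 files to fall on 14 different days, can be reported as optional sensitivity summaries. Neither corrects an error, because the article states that no dosage is established.

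The cost is a few lines of wording and a scoring rule. The opening and closing time stamps for each app feature, described under centralized data management, are already collected. The result may look less favourable than the mean, and it will be imprecise: with an assumed 25 per arm, 12 of 25 (48%) has an exact 95% confidence interval of 27.8% to 68.7%. It should be reported with its interval.
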